## Abstract

**Background:**

Health care services are being challenged by an increasing number of patients and limited resources. Hence, research investigating options to reduce costs and increase effectiveness is warranted. Digital outpatient services can provide flexible and tailored follow-up, improve patients’ health literacy, and facilitate the identification of adverse courses of disease. However, previous research largely focused on disease-specific contexts and outcomes. Therefore, research on digital services investigating generic outcomes such as health literacy is warranted.

**Objective:**

This article aims to describe the “digital outpatient service” intervention and present the protocol for an ongoing multicenter, nonrandomized trial evaluating this intervention.

**Methods:**

Based on previous experiences and evidence-based knowledge, we developed this intervention through patient-journey maps in collaboration with each clinical specialty. The patients gain access to a mobile app for self-monitoring and patient-reported outcomes and a chat for contact between the patients and health care workers. The health care workers’ dashboard includes a traffic light system to draw attention to the most urgent patient reports. In this multicenter, non–randomized controlled trial, patients are allocated to the control group receiving standard care or the 6-month intervention. Eligible patients are aged 18 years or older who receive outpatient care at the neurology, lung, pain, or cancer departments at 2 university hospitals in Norway. Our evaluation will include patient-reported outcomes, qualitative interviews, and clinical measures. The primary outcome will be health literacy using the Health Literacy Questionnaire. A sample size of 165 participants is split into a 1:2 ratio in favor of the intervention. We will analyze quantitative data in SPSS (IBM Corp) using descriptive statistics and logistic regression, and qualitative data using thematic analysis.

**Results:**

This trial started in September 2021, and the intervention started in January 2022. Recruitment has ended, with 55 patients in the control group and 107 patients in the intervention group. Follow-up is expected to end in July 2023, with results expected to be obtained in December 2023.

**Conclusions:**

This study will evaluate an intervention facilitated by an already certified digital multicomponent solution, with intervention content based on patient-reported outcomes, health literacy, and self-monitoring. The intervention is specifically tailored to each participating center and the needs of their patients using patient journey maps. The comprehensive and generic evaluation of this digital outpatient service intervention is a strength as it targets a heterogeneous sample of patients. Thus, this study will provide important knowledge about the applicability and effects of digital health care services. As a result, patients and health care workers will gain a new, evidence-based understanding of whether and how digital tools may be used in clinical care.

**Trial Registration:**

ClinicalTrials.gov NCT05068869; https://clinicaltrials.gov/ct2/show/NCT05068869

**International Registered Report Identifier (IRRID):**

DERR1-10.2196/46649

## Introduction

While advanced medicine contributes to prolonged life expectancy, the number of patients increases, and health service resources remain limited [1]. The reduction in hospital overnight capacity often increases the number of outpatient consultations. There is a risk of suboptimal resource use in current health services as these do not sufficiently meet individuals’ needs for understandable health information [2,3]. Digital health solutions, which have emerged over the last decades, are embraced and called for by health authorities [4,5], and the recent COVID-19 pandemic has led to a fast, large-scale adoption [6]. Systematic reviews provide some evidence about the effects of digital solutions [7-9], but the extent to which digital services can improve patient outcomes or resource use has not been firmly established [10].

Any implementation of digital health solutions requires patients’ and health care workers’ understanding of why and how the digital possibilities are used [11,12]. Thus, it is necessary to attain a certain level of health literacy, defined as “the cognitive and social skills that determine the motivation and ability of individuals to gain access to, understand, and use information in ways which promote and maintain good health” [13]. Health literacy is closely related to patients’ self-management and decisions related to their health [14], and eHealth literacy is linked to the use of digital solutions for health [12]. Low health literacy is associated with poorer health outcomes [15], lower self-management, and less use of digital health solutions [2,16]. It is reasonable to expect that better health literacy will improve self-management and the ability to benefit from digital health solutions [12]. The paucity of systematic reviews supports research focusing on the possibilities of digital interventions on health literacy [12,16].

Digital health solutions have embraced the use of patient-reported outcome measures (PROMs), allowing patients to subjectively report their health, pain, symptoms, and other relevant parameters [17]. PROMs allow health care workers to individualize patient care, although it has been challenging to demonstrate clinical effects in research [18]. However, effect evaluations should be part of studies on how PROMs are used in a clinical setting, and explanatory factors should be identified [19-21]. When routinely used, PROMs may support self-management and communication between patients and health care workers [17,19].

Allowing patients to digitally engage, self-monitor, and share data with health care workers has some obvious advantages and challenges [16,20,22,23]. From both the patient’s and the health care worker’s perspectives’, digital solutions must be usable, clinically relevant, convenient, and evidence based. Patients rely on health care workers to assess their data; likewise, health care workers depend on patients to report the assigned health parameters without under- or overreporting symptoms [24]. Digital solutions in outpatient care may contribute to the prevention of complications or exacerbations by promoting contacts between patients and health care workers, allowing the latter to intervene earlier and to act according to clinical needs [25]. A recent systematic review found that using digital solutions increased patients’ engagement in the technical usability of the solutions that affected their everyday lives [26]. Patients were also found to report more confidence in and knowledge of their own conditions and increased autonomy. These findings support those of earlier research on patients’ engagement and the impacts of digital solutions [27].

There is limited research regarding the development and impacts of multicomponent digital solutions that include PROMs, remote monitoring, patient notifications, alerts for health care workers, asynchronous chats, and video consultations. An evaluation of a heterogenous range of digital health interventions found some positive effects on coping, quality of life, and pain in cancer treatment [28], as well as alleviation of both pain and functional disabilities in disorders associated with musculoskeletal pain [29]. Primary research in home monitoring of symptoms enables detection of exacerbations and progression in patients with interstitial lung disease (ILD) [30], but there is a need for evidence to support new ILD interventions [31]. There has been wide adoption and positive effects of mobile apps for patients with epilepsy, although less so in collaboration with health care workers [32]. The need to study homogeneous, static, and standardized interventions with a high level of fidelity [33] might explain why research on digital solutions is rarely conducted despite the frequency of their application in clinical care. Furthermore, clinical challenges remain, particularly regarding the integration of electronic health records into existing platforms [22]. There is limited knowledge about how digital systems fit current workflows and about how data and PROMs should be standardized to best generate registry data of value for other clinical sites and researchers [16,23]. Altogether, there is a paucity of empirical studies on the implementation and impacts of digital health solutions on outpatient care.

The purposes of this article are to (1) describe the digital outpatient service intervention and how it promotes digital outpatient care, and (2) present a multimethod protocol for a multicenter, nonrandomized trial to evaluate the intervention.

## Methods

In the following, the development of the digital outpatient service intervention is presented before the details of the planned trial. The aim of the planned trial is to evaluate whether this intervention can have positive impacts on outcomes, including health literacy, health-related quality of life (HRQL), digital health literacy, satisfaction, and use of health service resources. Qualitative interviews will provide in-depth knowledge about the intervention from the perspectives of patients and health care workers. Furthermore, possible care pathways that ensure the quality of care and efficiency of remote monitoring in digital outpatient care will be investigated. The reporting of the intervention was guided by the Template for Intervention Description and Replication (TiDiER) [34], the protocol is reported according to the SPIRIT (Standard Protocol Items: Recommendations for Interventional Trials) [35], and the PROMs are reported according to the SPIRIT PRO extension [36].

### Development of the Digital Outpatient Service Intervention

#### Participants in the Development of the Intervention

The intervention was developed through collaboration among researchers from the Oslo University Hospital (OUH) intervention center, product managers at Dignio Connected Care, and health care workers and health care researchers from each participating department. These include the Department of Respiratory Diseases, the Department of Neurology, and the Department of Pain Management at OUH, as well as the Department of Cancer at the University Hospital of North Norway (UNN). To achieve an intervention suitable for patients’ needs and available staffing resources, each department tailored the intervention to their patient group and organizational structure.

#### Patient and Public Involvement

Representatives from the Norwegian Cancer Society contributed to the project’s development. Furthermore, the intervention for the neurology department is based on content developed together with patients and stakeholders. Health care workers are included as they constitute significant users in this project. The MyDignio app has been through several patient reviews before the current version.

#### Essential Elements and Aim of the Intervention

At the core of the intervention in all 4 departments is increased access to outpatient services. On the digital platform, patients can respond to PROMs and self-monitor parameters relevant to their conditions and have asynchronous, easy-access contact with health care workers. Designated health care staff will assess these data and act accordingly. These elements may facilitate flexible patient follow-up, building on a conceptual model that explains associations between health literacy and health outcomes, such as access to services, use of services, interactions between patients and health care workers, and patient self-care [37]. Patients can have an increased influence on their care and their contact with health care services through self-reported subjective experiences related to their care needs and their wishes for follow-up, in combination with their reports of objective measures such as blood pressure or oxygen saturation. This may facilitate timely contacts between patients and health care workers, where patients can receive guidance based on their questions, and likewise enable health care workers to identify patient struggles more accurately.

#### The Digital Platform for the Intervention: Dignio Connected Care

The platform for the digital outpatient service intervention is Dignio Connected Care [38], consisting of the multicomponent cloud-based system Dignio Prevent for health care workers and the MyDignio patient app. It is CE (Conformité Européenne: French for “European conformity”) marked, satisfies all regulatory requirements for privacy and information security, and has been used in various clinical settings in Norway [39-41], the United Kingdom [42], and China [38]. The digital platform can be tailored to the needs of individual patients in consultation with their health care workers. Components can be added to individualize follow-ups (Tables 1 and 2) and will vary depending on the treatment at any given time. Examples of the interface are given in the Multimedia Appendices 1 and 2.

**Table 1 table1:** Patient-reported components used in the digital outpatient service.

Dignio component			Short description		Center using the component in its intervention	
Patient-reported outcome measures (PROMs)			Standardized and individualized PROMs with numerical scales, single and multiple-choice answers, and free text.		Cancer: Edmonton Symptom Assessment System (ESAS-r) [43], Eastern Cooperative Oncology Group (ECOG) scale assessing functional level [44], PROM version of the Common Terminology Criteria for Adverse Events (PRO-CTCAE) [45] and items on side effects of chemotherapy. The frequency of administration is per individual needs. Lung: King’s Brief Interstitial Lung Disease questionnaire (K-BILD) [46] assessing self-reported health every 12th week, and items on side effects (vomiting, rash, dizziness, abdominal pain, or diarrhea), administered every 4th week. Neuro: PRO-EPI: A multidimensional epilepsy PROM with items on seizures, medication, living with epilepsy, and need for health services developed by clinicians and the Norwegian Epilepsy Network for health care workers [47,48], administered every 11th week. Pain: Items on pain on a visual analog scale, intensity, location, side effects (constipation, sweat, anxiety, etc), compliance with current treatment and need for health services, administered per medication plan when changes to this plan are made.	
**Physiologic measures**						
	Blood pressure	Bluetooth devices or BYOD^a^		Cancer, on clinical indication		
	Body temperature	Bluetooth devices or BYOD		Cancer, on clinical indication		
	Body weight	Bluetooth devices or BYOD		Lung, weekly		
	Spirometry values	Bluetooth device		Lung, weekly		
	Oxygen saturation	Bluetooth device		Lung, weekly		
	Pulse	Bluetooth devices or BYOD		Lung, weekly		

^a^BYOD: bring your own device.

**Table 2 table2:** Functionality for remote monitoring and communication.

Dignio component			Brief description
Tasks			Health care workers can specify tasks for patients, such as performing daily activities, registering measures taken with the patients’ own devices, or watching patient videos.
Thresholds			Health care workers can define thresholds. The limit values are set, based on each patient’s baseline, and follows the traffic light model, with green, yellow, and red alerts.
Notifications and triage			When measures are outside defined thresholds, health care workers are notified. Deviating values, responses, and unanswered messages from patients are captured by an overview of patients in Dignio Prevent, where they are sorted by degree of urgency or severity (traffic light model). If the patient does not perform the defined tasks at the specified time, a warning is triggered. This can admittedly be turned off if desired.
Reminders			Reminders can be sent to the patients as push-notifications in MyDignio, through email or SMS texts. When the task or measure is done, the reminders stop.
Messages or chat			Patients and health care workers can send messages to each other and have an asynchronous dialogue when it is best for both parties. Lung: patients are asked to upload photos of the results of any laboratory tests conducted and the results of a 6-minute walking test conducted at their local hospital every 12th week. Neuro: patients are allowed to upload photos of seizures whenever relevant.
Video consultations			A video consultation can be arranged if needed. A video room is created with an encrypted connection where the patient and health care worker can meet.
Information pages			MyDignio has an information page that can be updated by health care workers from the web portal Dignio Prevent. It is possible to create an individual information page, create templates, and send updates to several patients.
**Efficacy tools (templates)**			
	Templates for patient care	Templates can be developed to facilitate a standardized follow-up at given times, allowing health care workers to monitor any changes in a timely manner.	

#### Patient Journey Maps

In collaboration with each department, patient journey maps have been drawn [49] to target the potential for a digital outpatient service and assess how the use of digital tools may affect patient outcomes, patient flow, and health care workflow. Common challenges, visualized through the red exclamation marks (Figures 1 and 2), include limited health care worker resources, an overwhelming number of patients, time-consuming telephone calls, and the challenge of contacting patients at risk (see Multimedia Appendix 3 for further examples). Patients may have a limited overview of their parameters, including PROMs and clinical data, compromising their health literacy and self-monitoring.

**Figure 1 figure1:**
[figure not shown]
Patient journey map from the neurology department: as-is.

**Figure 2 figure2:**
[figure not shown]
Patient journey map from the neurology department: to-be.

#### Information and Training

The patients receive a brief introduction and digital user manuals for the app. Patients using technical equipment such as spirometers are instructed to ensure correct technique and synchronization with MyDignio. Patients in the intervention group can contact their health care worker or a researcher for technical inquiries.

Most of the health care workers are familiar with the platform as they are involved in the development of the individual interventions at each center. All new health care workers receive training by the Dignio personnel or the assigned administrator at their center, and the training will be repeated upon request. Training in interpreting scores reported by the patients is provided within each department based on the needs of the health care workers. For the majority of the involved health care personnel, the PROMs applied are already used paper-based in the clinics; thus, a dialogue between the programmers from Dignio Connected Care and the health care workers has facilitated the use of already standardized cutoffs.

Implementation is secured through the involvement of dedicated health care workers within each department that contributed to the development of the intervention, the summarizing of the “as-is,” and the potential and suggestions of the “to-be” that had received training in the digital platform. In addition, designated health care workers were compensated for 10%-20% of their time to contribute to the intervention.

### Study Design for the Planned Trial to Evaluate the Intervention

The study is a multicenter, non–randomized controlled trial with 2 treatment arms and a 6-month follow-up (Figure 3). The comprehensive evaluation is based on the method for assessment of telemedicine (MAST) [50], including elements regarding the purpose and maturity of the technology, how the health problems align with the technology, safety, clinical effectiveness, patient perspectives, economic aspects, organizational, and sociocultural, ethical, and legal aspects, followed by an assessment of cross border between countries, transferability, and generalizability to other contexts. The relevance of MAST lies in its thorough assessment of the preceding conditions and its multidisciplinary assessments. Patients are currently allocated to 1 of the 2 arms. At each department, recruitment to the control arm will be completed before inclusion in the intervention arm. The control arm will receive follow-up *per the* routines at each department, largely as described in the patient journey maps labeled “as-is” (Figures 1 and 2, and Multimedia Appendix 3). The intervention arm will receive our digital outpatient service. Quantitative measures are collected longitudinally, and qualitative interviews are conducted postintervention.

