### Patient Participants and Recruitment

Patients at the Department of Respiratory Diseases, the Department of Neurology, and the Department of Pain Management at OUH, as well as the Department of Cancer at UNN, are eligible for participation in the study if they are 18 years of age or older, home-based, and able to fill out Norwegian questionnaires (Table 3). Both newly diagnosed or newly referred patients, those with a diagnostic history, and those already in outpatient care are eligible for inclusion.

Eligible patients are identified through an outpatient consultation or through patient lists. All patients receive written and oral information about the project from a nurse or physician before giving their consent. The patients are not regarded as consenting participants until they have signed the consent form and filled out the baseline questionnaire. To reduce contamination in the intervention arm, patients must consent and fill out the baseline questionnaire before accessing the digital intervention.

The recruitment of patients to the qualitative interviews after the intervention is based on their consent to receive information regarding the interviews. Purposive sampling is applied to reach a heterogeneous sample with a balanced diversity in age, gender, and use of the intervention. Thus, in-depth knowledge can be obtained from both high and low users.

**Table 3 table3:** Eligibility criteria for patients.

Patient groups	Inclusion criteria	Exclusion criteria
Patients with cancer	Cancer Receiving active treatment	Life expectancy: less than 6 months Expected need for follow-up: less than 6 months
Patients with interstitial lung disease (ILD)	ILD	Very low degree of function with risk of cognitive influence
Patients with epilepsy	Epilepsy	Complex causes of epilepsy Severe comorbidity Other planned or ongoing assessment and treatment, including assessment of unexplained illness or testing of medication
Patients with long-term, complex pain	Drug testing, adjustment, and dose reduction Self-administering medication	Comorbidity that directly affects the drug adjustment Interference with other ongoing treatment Cognitive impairment Not living at home

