### Randomization and Blinding

This is a non–randomized controlled trial without blinding. Both patients and health care workers are familiar with the treatment arm to which the participants belong during the study.

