### Analysis

#### Statistical Analysis

The baseline and follow-up variables will be presented descriptively. Continuous variables will be analyzed using the mean and the SD for normally distributed data and the median and the range if the data are skewed. Categorical data will be presented as counts and percentages. The mean change will be estimated by subtracting the baseline score from the follow-up score, both at 3 months and 6 months. Differences in mean changes in short-term and long-term variables will be modeled using a one-way ANOVA. To adjust for possible confounders, logistic regression models will include age, gender, education, and hospital department. Missing data will be handled according to the syntax and protocol of the standardized instruments, such as HLQ, eHLQ, SUTAQ, and RAND-12. The missing data in terms of dropout has been accounted for in the power analysis.

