This intervention will support and enhance patients’ understanding of health information well enough to know what to do, make them feel understood and supported by health care workers, ensure that they have sufficient health information, support their feeling of actively managing their health, and improve their ability to interact with health care workers. These actions are directly transferable to the HLQ and this study’s outcome domains [51]. Additionally, the intervention will support patients’ use and understanding of digital solutions for health and thus their engagement, as well as ensure their access to digital solutions that work, suit their needs, and keep their health data secure, all of which are transferable to digital health literacy [12,53]. Altogether, this intervention will target and measure the domains of health literacy skills at the basic, communicative, and critical levels [14]. This study will also consider factors that are affected by external factors in health care services and the internal factors held by the patient. As this intervention will be individualized according to each patient’s needs, it can facilitate health actions and lead to an increase in health literacy.

This study describes how the digital outpatient service intervention will be explored in a multicenter, nonrandomized controlled trial with 2 treatment arms and a 6-month follow-up. The strengths of the current trial include its focus on patient-reported health literacy in a digital health intervention that targets a diverse sample of outpatients. Previous interventions have tended to focus on a single component, target a very specific sample, and primarily use clinical end points. Whether or not a patient chooses to use a digital intervention perhaps relies more on their health literacy and motivation to self-monitor, and a positive change in clinical end points may primarily be perceived as a potential result of their health literacy levels and self-monitoring. Moreover, the multimethod design inspired by the MAST [50] will provide quantitative data on the effects of the intervention on health literacy and in-depth qualitative knowledge on the acceptability of the intervention among patients and health care workers. Overall, the proposed trial will evaluate the effects while providing an understanding that can facilitate lasting changes in how outpatient specialty health services use digital solutions.

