The proposed trial is designed as a nonrandomized trial, which inherently includes some risk of bias. Thus, differences may occur between the control group and the intervention group. The groups will therefore be compared at baseline to detect any imbalances that would need handling in the statistical analysis. Changes in outcome measures will be calculated based on the change from baseline to follow-up, thus handling the fact that individuals might have a different baseline score. Further, we did not pilot the intervention within each group before the full trial, which could have revealed weaknesses relevant to the full trial. Lastly, the outcomes measured by standardized questionnaires have not been used to screen for any need for a more tailored intervention. That is, it could have been relevant to tailor the intervention based on the participants’ scores in health literacy or digital health literacy. Individual health care workers have individualized patient follow-up based on the patients’ needs, but not through systematic screening. Also, we do not have data on the occurrence of any comorbidities in the sample, which could have been a relevant confounder added to the already described ones. No patients were specifically involved in the development of this intervention or the design of this trial. However, the intervention toward patients with epilepsy was developed alongside user representatives before this study.

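### The arms are consecutive cohorts within each department, but adjustment covers only four variables, and any other imbalance is left to an unspecified baseline comparison and change scores

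*Protocol article*

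**What the plan says.** On allocation, Randomization and Blinding states: "This is a non–randomized controlled trial without blinding". The Study Design section adds: "At each department, recruitment to the control arm will be completed before inclusion in the intervention arm". The abstract's Results give the calendar: "This trial started in September 2021, and the intervention started in January 2022". They also give the numbers enrolled: "Recruitment has ended, with 55 patients in the control group and 107 patients in the intervention group".

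On analysis, the Statistical Analysis section compares mean changes from baseline by one-way ANOVA and names no covariate there. Confounder adjustment appears only in this form: "logistic regression models will include age, gender, education, and hospital department". The Discussion accepts that the design carries a risk of bias and offers two safeguards. One is the use of change scores. The other is this: "The groups will therefore be compared at baseline to detect any imbalances that would need handling in the statistical analysis". The article does not say which variables are compared, what counts as an imbalance, or what is then done.

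On data, Tables 4 and 5 show that several further variables are recorded at T0: HLQ domain 9 itself, all seven eHLQ domains, use of smartphone, tablet and computer, use of health apps, time since diagnosis, and COVID-19 infection and fear. None is in the named adjustment set.

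**The concern.** Within a department, every control patient was enrolled before any intervention patient. Anything that drifted over the recruitment period therefore differs by arm. This could be case mix, familiarity with digital care, pandemic conditions, or which patients staff approached once the app was on offer. Case mix has room to drift, because eligibility is broad: "Both newly diagnosed or newly referred patients, those with a diagnostic history, and those already in outpatient care are eligible for inclusion". The Discussion also raises a possible link between the outcome construct and willingness to use the service: "Whether or not a patient chooses to use a digital intervention perhaps relies more on their health literacy and motivation to self-monitor".

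Age, gender, education and department do not directly measure digital readiness, disease duration or the starting level of health literacy. Any such difference that predicts change in HLQ domain 9 would be read as an effect of the service. Change scores remove a fixed difference in level. They do not remove differences in trend or the influence of other variables, and they leave regression to the mean if baseline HLQ domain 9 differs between cohorts.

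**Working it through.** The article gives no figure for confounding, so there is none to reproduce. The checks ask how well the stated safeguards would work.

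**Inputs from the article.** Enrolled 55 and 107 (abstract). Planned 55 and 110, SD 0.6, target difference 0.5, dropout 20% (Sample Size). SD 0.77 is the largest of the three source SDs listed there.

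**Assumed inputs.** Two-sided 5% level (the article states two-sided but no level). The baseline comparison is a significance test. Imbalances are 0.2 to 0.4 SD. Each confounder correlates 0.3 with the analysed outcome.

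**1. Chance that a baseline test flags an imbalance.**
- SE of a standardized difference = √(1/55 + 1/107) = 0.166.
- Power ≈ Φ(d/SE − 1.96).
- d = 0.2: Φ(1.21 − 1.96) = 23%.
- d = 0.3: Φ(1.81 − 1.96) = 44%.
- d = 0.4: Φ(2.41 − 1.96) = 67%.

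A 0.3-SD imbalance is missed more often than found.

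**2. Shift caused by a missed imbalance.** Shift = imbalance in SD × standardized coefficient × outcome SD.
- One confounder: 0.3 × 0.3 × 0.6 = 0.054, about 11% of 0.5.
- Three mutually independent, all in the same direction: 3 × 0.054 = 0.16, about a third of 0.5.
- Three that correlate 0.5 with one another: each coefficient falls to 0.3/(1 + 2 × 0.5) = 0.15, and the total is 3 × 0.3 × 0.15 × 0.6 = 0.08, about 16% of 0.5.

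Overlap with age and education, which are already named, would lower these further.

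**3. Effect on the test when there is no true effect.** With 20% dropout the planned numbers leave 0.8 × 55 = 44 and 0.8 × 110 = 88. SE = 0.6 × √(1/44 + 1/88) = 0.111. The rejection rate for a shift b is 1 − Φ(1.96 − b/SE) + Φ(−1.96 − b/SE).

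| Shift b | SD 0.6 | SD 0.77 |
|---|---|---|
| 0.05 | 7% | 6% |
| 0.10 | 15% | 11% |
| 0.15 | 27% | 18% |

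Modest uncorrected shifts are enough to raise the nominal 5% error rate.

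**4. What adjustment can reach.** Covariates act on measured differences between patients. Within a department, arm and enrolment period coincide, so no patient covariate separates them. Calendar time could be partly separated only across departments, and only if they switched arms at different dates. The article gives one intervention start, January 2022, and no dates by department.

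**The case against.** The strongest reply is that the article already concedes bias, promises to handle imbalances found at baseline, and mentions room for controlled analyses in its sample size. On that view the details belong in a fuller plan that is not shown. It is true that the article does not rule out later use of the T0 variables, so a reader who infers that they will go unused goes too far. What stands is that the article itself names an adjustment set and a route for extending it, and that route depends on the data and is weak at this size.

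Two other stronger readings are tempting but unsupported:

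- **The intervention arm selected digitally able patients.** The Data Security section describes digital consent and web questionnaires behind a government ID login, without distinction by arm. Controls therefore seem to have passed a digital threshold too. That narrows this route, although willingness to use an app may still differ. It also means that yes/no device use may vary little.
- **The protocol says that take-up depends on health literacy.** The Discussion sentence is hedged and general, and it does not describe enrolment. Likewise, the mix of new and established patients is allowed in both arms, and nothing shows that it differed.

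The choice of covariates is also partly judgement. No passage links COVID-19 fear to HLQ domain 9. The article acknowledges overlap between eHLQ and HLQ domains, so one eHLQ domain beside baseline HLQ domain 9 is enough.

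**Conclusion.** The point holds as a weakness in how confounding is controlled. With consecutive cohorts, four named covariates, change scores and an unspecified baseline comparison do not reliably deal with differences between arms. The 44% figure rests on reading the comparison as a 5% significance test, which the article does not say.

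The shifts of about 0.05 for one confounder, and 0.08 to 0.16 for three, rest on assumed imbalances and correlations. The 0.16 further needs three independent confounders that all act in the same direction. A reader might take 0.16 as the expected bias, but the article gives no data on the size or direction of any bias.

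A reader might also infer that a longer covariate list would make the comparison free of time trend. It would not: it reduces measured selection only, and the calendar limitation remains after any adjustment.

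**What to change.** Before analysis, and regardless of any baseline comparison, specify one linear model for HLQ domain 9 at follow-up. Include arm, baseline HLQ domain 9, age, gender, education, department, time since diagnosis and one T0 measure of digital readiness. A single eHLQ domain suits the last of these, since it is likely to vary more than yes/no device use. T0 COVID-19 fear can be an optional covariate in a sensitivity analysis. Use T0 values only, because later values may be affected by the intervention. Keep the baseline table for description, not for choosing covariates.

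State that the covariates reduce measured selection but cannot separate the service from calendar time within a department. Word the conclusion as an adjusted difference between consecutive cohorts. Add a sensitivity analysis with enrolment period only if the departments' switch dates differ, and report those dates.

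The cost is a change of analysis wording. No new data are needed. Baseline HLQ domain 9, time since diagnosis and one eHLQ score add three parameters if each enters linearly, against 44 + 88 = 132 planned completers. An enrolment-period analysis would have a wider confidence interval.
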